### 8.3 Exclusion Criteria

Subjects will not be included in the study if any of the following criteria applies:

- Subjects is not able to give consent
- Onset of ataxia in association with stroke, encephalitis, sepsis, hyperthermia or heat stroke

- Toxic causes for ataxia of cerebellar type
- Rapid progression of ataxia (development of severe ataxia in less than 12 weeks)
- Subject suffers from any of the following:
  - chronic diarrhea
  - unexplained visual loss
  - malignancies
  - insulin-dependent diabetes mellitus
- Ataxia due to multiple sclerosis, ischemia, hemorrhage or tumor of the posterior fossa as confirmed by imaging
- Ataxia due to clinical likely multisystem atrophy type C (MSA-C)
- Diagnosis of clinical likely Friedreich ataxia
- Known history of hypersensitivity to the investigational drug or derivatives
- Liver failure defined as AST/ALT > 300 U/l
- Simultaneous participation in another clinical trial or participation in any clinical trial involving administration of an investigational medical product within 30 days prior to the beginning of the clinical trial
- Subjects with a physical or psychiatric condition which at the investigator's discretion may put the subject at risk, may confound the trial results, or may interfere with the subject's participation in this clinical trial
- Known or persistent abuse of medication, drugs or alcohol
- Females of childbearing potential, who are not using and not willing to use medically reliable methods of contraception for the entire study duration as listed in the patient informed consent form
- Current or planned pregnancy or nursing women
- Patient has received any of the following prohibited medication within 4 weeks prior to randomization
  - Aminopyridines (including sustained-release form)
  - Acetyl-DL-Leucine
  - Riluzole
  - Gabapentin
  - Varenicline
  - Chlorzoxazone

The indication specific exclusion criteria are chosen based on the available data on Acetyl-DL-Leucine of the French Agence nationale de sécurité du médicament et des produits de santé (<http://agence-prd.ansm.sante.fr/php/ecodex/notice/N0126720.htm>, visited at 24.04.2015, dated on 20.02.2007), in particular hypersensitivity to the agent.

#### 8.4 Subject Information and Recruitment

If a subject appears to be eligible for the trial, the investigator will inform the subject about the trial and ask the subject or in case of subjects without legal capacity the legal representative/authorized agent for his/her written consent.

It is a requirement that written consent is obtained prior to any trial-specific procedure.

#### 8.5 Randomization and allocation concealment

All patients who give consent for participation and who fulfill the inclusion criteria will be randomized.

Randomization is requested by the staff members responsible for recruitment at the trial centers.

The randomization number consists of a consecutive three-digit tracking number (so called package number). The patient identification number results from a combination of the trial center number and the package number.

Concealed randomization to both treatment sequences (Verum->Placebo; Placebo->Verum) will be performed with a 1:1 allocation ratio. The allocation sequence will be generated by an independent person of the Institute for Medical Informatics, Biometry and Epidemiology (IBE) of the University of Munich not involved in assessing the outcomes of the study. Neither the investigators nor the patients will be informed about the treatment sequences to which a patient is allocated, and neither can get access to the randomization list. The randomization is based on a permuted balanced block design with random block length. The procedure considers stratification by center and by 'genetically' vs. 'sporadic' cerebellar ataxia.

According to this pre-specified randomization list provided by the IBE the trial medication kits will be signed out with (consecutive) identification numbers. An opaque sealed envelope containing the corresponding treatment sequence for unblinding in the case of an emergency will be attached. Hence, the investigator can unblind a single patient at any time. All envelopes have to be sent back to the DSGZ/sponsor-delegated person at the end of the trial. Each trial center receives a pool of trial kits. The package numbers for the kits stored at each center will be registered at the IBE. The IBE will provide the internet-based randomization tool "Randoulette" (<https://wwwapp.ibe.med.uni-muenchen.de/randoulette/>) which assigns one of the trial kits stored at the respective center when a new patient fulfils the inclusion criteria. In this way, an immediate registration and randomization of enrolled participants is guaranteed. Furthermore, the amount of trial kits stored at the centers can be checked continuously. Replacement of the trial kit is only possible after contact and organization with the Study Center of the DSGZ and the Randoulette team.

**Confidential**

## 9 Investigational Medicinal Product (IMP)

### 9.1 Specification of IMP

#### IMP 1: *Acetyl-DL-Leucine* (TANGANIL®)

|                                           |                                                                                                                                                                                                                                                                      |
|-------------------------------------------|----------------------------------------------------------------------------------------------------------------------------------------------------------------------------------------------------------------------------------------------------------------------|
| Drug name                          | TANGANIL®                                                                                                                                                                                                                                                            |
| Name of manufacturer               | Pierre Fabre, Castres, France                                                                                                                                                                                                                                        |
| Substance name                     | Acetyl-DL-Leucine                                                                                                                                                                                                                                                    |
| Dose of active ingredient per unit | 500 mg                                                                                                                                                                                                                                                               |
| Other ingredients                  | Wheat starch, pregelatinized corn starch, calcium carbonate, magnesium stearate                                                                                                                                                                                      |
| Pharmaceutical form                | Tablets                                                                                                                                                                                                                                                              |
| Mode of administration             | Oral                                                                                                                                                                                                                                                                 |
| Storage conditions                 | Do not store > 25°C.

The drug tablets will be reblistered from original blisters and packaging boxes and relabeled. All procedures will be performed under sterile conditions. All procedures will be performed the pharmacy of the University of Heidelberg. |

IMP 1 is already used as a marketed product (TANGANIL®) in France, Congo, Tansania and Vietnam. The IMP 1 will be purchased from Pierre-Fabre and then delivered and supplied to the trial centers by the Pharmacy of Heidelberg University – together with the corresponding placebo. The TANGANIL® tablets will be refilled from the original packaging to blister under sterile conditions and study specific labels applied, these blisters are in a pack. These procedures will be performed by the Pharmacy of Heidelberg University.

**Confidential**

**IMP 2: Corresponding Placebo**

|                                           |                                                                                 |
|-------------------------------------------|---------------------------------------------------------------------------------|
| Drug name                          | Placebo                                                                         |
| Name of manufacturer               | Haupt Pharma Wuelfing GmbH                                                      |
| Substance name                     | NA                                                                              |
| Dose of active ingredient per unit | NA                                                                              |
| Other ingredients                  | Wheat starch, pregelatinized corn starch, calcium carbonate, magnesium stearate |
| Pharmaceutical form                | Tablets                                                                         |
| Mode of administration             | Oral                                                                            |
| Storage conditions                 | Do not store > 25°C.                                                            |

Placebo will be an identically appearing tablet and visually indistinguishable from TANGANIL®. Placebo bulkware will be manufactured and released by Haupt Pharma Wuelfing GmbH and send to the Pharmacy of Heidelberg University for study specific primary and secondary packaging.

**9.2 Packaging and Labelling of IMP**

The carton box with the IMP will be labeled as follows (according to Annex 13, GMP):

- Name, address and telephone number of sponsor
- Name, address and telephone number of manufacturing / packaging pharmacy
- Name of the drug: Acetyl-DL-Leucine/Placebo
- Other Ingredients
- mode of application, dosage form, quantity of dosage units, strength
- Charge identification (Ch.-B.)
- Package number
- Treatment phase
- Protocol Code ALCAT
- EudraCT No. 2015-000460-34
- Expiry date
- Instructions for storage: do not store > 25 °C
- Note: For clinical trial use only
- Note: keep out of reach of children

**Confidential**

The blister will be labeled with the minimum particulars according to Annex 13, GMP. The labeling will be in German and in Dutch.

### 9.3 Transport of IMP

Distribution and shipment of Acetyl-DL-Leucine and the corresponding placebo to the trial centers will be organized by the Pharmacy of Heidelberg University. A temperature control during transport is not necessary.

### 9.4 Storage requirements

The following storage conditions have to be kept for the IMP(s):

Acetyl-DL-Leucine (TANGANIL®) and Placebo: Do not store > 25°C

The investigator is responsible for ensuring adequate storage and sufficient stock supply of the IMP(s) at the center in a secure location at the site, preferably in a lockable cabinet with restricted access to the investigator(s) and authorized site staff. Personnel who have access to the trial drug need to be listed (name and responsibilities) on the Team Delegation Log in the trial specific Investigator Site File (ISF).

The investigator should ensure that the IMP is only used according to the protocol.

Temperature has to be recorded continuously using a Min-Max-Thermometer. These recordings have to be controlled weekly, the results have to be documented in a temperature log by an authorized person.

### 9.5 Dosage, Mode of Application and Dose Schedule

- Strength: 500 mg Acetyl-DL-Leucine/ Placebo
- Mode of application: oral intake
- Duration of treatment: 6 weeks
- Dose schedule
 

|          |               |       |
|----------|---------------|-------|
| Week 1   | 1.5 g per day | 1-1-1 |
| Week 2   | 3 g per day   | 2-2-2 |
| Week 3-6 | 5 g per day   | 3-3-4 |

The primary packing of the study medication are blisters, the secondary packaging a carton box – one for each treatment phase.

The medication has to be taken at least 30 minutes before and at least 2 hours after a meal.

**Confidential**

## 9.6 Handling of IMP at the Site and Drug Accountability

The packaged IMP(s) provided by the Pharmacy of Heidelberg University has to be stored in a secure location at the site, preferably in a lockable cabinet with restricted access to the investigator(s) and authorized site staff. Personnel who have access to the trial drug need to be listed (name and responsibilities) on the Team Delegation Log in the ISF. In accordance with all applicable regulation requirements, the investigator is responsible for the IMP / randomized therapy accountability, reconciliation, and record maintenance on appropriate forms. The investigator is responsible that the complete and intact receipt of the total quantity of the IMP is ensured and documented as well as the correct storage of the IMP (see also section 9.4).

The investigator should ensure that the IMP is only used according to the protocol, and may only dispense the IMP to subjects who have signed the informed consent and who have been randomized in the trial. The dispensing of the investigational medicinal product to subjects outside of this clinical subject is not permitted.

The monitor will check the complete documentation during the regular monitoring visits and will clarify potential discrepancies between usage and dispensing of the IMP(s). The investigator or the monitor has to inform the sponsor-delegated person or the coordinating investigator in case of deficiency regarding e.g. storage or accountability of the IMP.

## 9.7 Procedures for Monitoring the Subject Compliance

Subjects are asked to take their trial drugs (used/empty and unused blister) with them at visit 3, 4 (first treatment period) and at visit 6, 7 (second treatment period). Unused medication has to be returned at visit 4 and visit 7. By counting the remaining tablets, treatment compliance with can be assessed. IMP dispense and return will be documented on the Drug Accountability Log to be filed in the ISF (copies should be send to the DSGZ in regular intervals). In the case of treatment discontinuation, the date of last intake and - if applicable - time periods without treatment will be recorded in the CRF.

## 9.8 Return and Disposal of IMP

The subject has to return the IMP at Visit 4 and Visit 7. All unused IMP is going to be destroyed on site. Destruction of IMP has to be documented on the Drug Accountability Log or the Final Site Drug Return and Destruction Log.

Copies of the forms completed at the trial site will be returned to the sponsor delegated person or the coordinating investigator at the end of the trial, and will be collected by the monitor during the close-out visit or sent to the sponsor-delegated person or the coordinating investigator on request. The original will remain on site.

## 9.9 Blinding and Emergency Codes

The trial will be subject and investigator blinded. Study personnel involved in patient recruitment and trial activities will have no access to the randomization list provided by the IBE. The statistician responsible for the final analysis will also have no access to the list.

## 9.10 Unblinding (Code break)

At the initiation of the trial, the trial site will be instructed on the method for breaking the blind (see 8.5). The actual allocation must not be disclosed to the patient and/or other study personnel including other site personnel, monitors, corporate sponsors or project office staff; nor should there be any written or verbal disclosure of the code in any of the corresponding patient documents.

### Early/ premature unblinding:

In general, breaking the blind should be considered only when knowledge of the treatment assignment is deemed essential for the study patient's care by the participant's physician or regulatory body. Unblinding should be restricted to emergency situations for reasons of subject safety, and is expected to be extremely rare in this trial. Unblinding should not necessarily be a reason for study discontinuation.

Where possible, it is important that all other members of the study team (e.g. other investigators, statisticians) remain blinded.

When the blinding code is broken the reasons must be recorded and documented on the case report form. Any unblinding will be documented in the study report.

Any of the following situations may be reasons for premature unblinding:

- In emergency situations, if it is necessary for the subject's safety, i.e. if the further treatment depends on the knowledge of the investigational medicinal product.
- In the event of accidental administration of the investigational medicinal product to a person who is not a subject.
- In the event of the death of a subject, if a causal relationship between the treatment with the investigational medicinal product and death is suspected.
- In the event of SAEs / SUSARs under certain conditions (causal relationship with the investigational medicinal product).

**Confidential**

The decision whether unblinding is necessary lies with the investigator.

### **Regular unblinding:**

As a matter of principle, unblinding happens regularly when the trial database is closed, after blinded data review following resolution of queries.

## **9.11 Prior and Concomitant care and intervention**

### **9.11.1 Previous therapy / medication of trial specific illness**

All previous therapies / medications applied over a period of 12 months before visit 1 will be documented in the subject's medical record and in the appropriate CRF.

### **9.11.2 Previous therapy / medication of other indications than the trial specific illness**

All previous treatments and medications for other indications than the trial specific illness occurred within the last 3 months before visit 1 of each patient will be documented in the CRF.

### **9.11.3 Prohibited concomitant therapy / medication for trial specific illness**

All other medication, which has been previously described to have a potential positive effect on cerebellar ataxia, in particular 4-aminopyridine, Riluzole, Varenicline, Gabapentin or Chlorzoxazone as mentioned in the exclusion criteria are not allowed to be applied during the trial.

Every effort should be made to avoid the use of any of the above listed prohibited therapies/medications during the entire duration of the trial and 4 weeks prior to treatment start.

If there is a single administration of any of the drugs mentioned above, the subject is still eligible for the main analysis. Regular intake of these drugs is considered a protocol violation (see protocol violations 13.5).

### **Role of physiotherapy and speech therapy**

Physiotherapy as well as speech therapy should not be started new while the subject is enrolled in the trial. If a patient is on physiotherapy and/or speech therapy 6 months prior to randomization, the amount (therapy hours per week) needs to be documented in the subjects' medical record and in the CRF and has to remain unchanged during the individual trial duration.

#### **9.11.4 Concomitant therapy / medication for other indications**

All concomitant therapies/medications other than the trial therapy/investigational medicinal product applied during the trial at the discretion of the investigator will be documented in the patient's records and will be documented in the CRF.

The doses of concomitant medications for e.g. chronic diseases should be kept as constant as possible throughout the trial. Concomitant medication will be recorded during whole individual study duration.

## 10 Trial Procedures

### 10.1 Methods of Assessment

The following section will give an overview and adequate explanations to the examinations and procedures to be performed in this trial. Source documents, including radiological imaging, if applicable, must be stored and be available for subsequent review. The respective printouts will be stored in the subject medical file.

#### 10.1.1 Scores for ataxia

The clinical severity of ataxia is assessed by different clinical scores. Specifically, the following two validated scores will be used:

- Scale for the assessment and rating of ataxia (SARA) [27]
- Spinocerebellar ataxia functional index (SCAFI) [28, 29]

Both scores assess ataxia of stance and gait, including gait speed as well as limb ataxia and dysarthria. Both scales are widely used in clinical practice [29] and treatment trials on cerebellar ataxia.[30, 31] Both scores cover the whole range of impaired motor function in ataxic patients.

The SARA serves as a key inclusion criterion for the severity of ataxia at the beginning of the study prior to enrollment. The SARA total score consists of 8 items reflecting neurologic manifestations of cerebellar ataxia. Each item represents a vital movement feature in cerebellar ataxia rated by an experimenter (gait, stance, sitting, speech disturbance, finger chase, nose-finger test, fast alternating hand movements, heel-shin slide) with a range of 4 – 8 points on each item resulting in a total score of 0 – 40 points. It is a reliable and valid clinical scale with a high internal consistency that measures the severity of ataxia and increases with ataxia disease stage.

Another clinical ataxia score, the SCAFI uses a timed approach evaluating the eight-meter-walking-time (8MW), the nine-hole-peg-test (9HPT) testing limb ataxia and the PATA-test for speech.

Equivalent to the SARA, the SCAFI also represents vital movement features (8 meter walking test; 9-hole-peg-test for evaluation of the coordination of the upper extremities; PATA-test for evaluation of speech). In contrast to the SARA, the SCAFI uses a timed approach rated by an experimenter. After the assessment, raw scores are transformed into reciprocals and converted into subtest Z-scores. The final SCAFI is then generated as the arithmetic mean of all three Z-scores. The scores will be measured at each visit.

The scores will be assessed by the investigators (see also Appendix section 22.1 and section 22.2).

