We reported in a case series on 13 patients with different types of cerebellar ataxia that the modified amino-acid Acetyl-DL-Leucine (5 g per day for one week) significantly improved the symptoms, measured by the Scale for the Assessment and Rating of Ataxia (SARA), the Spinocerebellar Ataxia Functional Index (SCAFI) and EuroQol-5D-5L; the agent was very well tolerated [10]. Mean total SARA decreased remarkably ( $p = 0.002$ ) from a baseline of  $16.1 \pm 7.1$  to  $12.8 \pm 6.8$  (mean  $\pm$  SD) on medication. There were also significant improvements in sub-scores for gait ( $p = 0.022$ ), speech ( $p = 0.007$ ), finger-chase ( $p = 0.042$ ), nose-finger-test ( $p = 0.035$ ), rapid-alternating-movements ( $p = 0.002$ ) and heel-to-shin-test ( $p = 0.018$ ). Furthermore, patients showed better performance in the SCAFI consisting of the 8-m-walking-time (8 MW,  $p = 0.003$ ), 9-Hole-Peg-Test of the dominant hand (9HPTD,  $p = 0.011$ ) and the PATA rate ( $p = 0.005$ ). Quality of life increased during treatment ( $p = 0.003$ ). No side effects were reported. In conclusion, Acetyl-DL-Leucine significantly improved ataxic symptoms without side effects and therefore showed a good risk-benefit profile. Videos documenting the effects can be found on the webpage of the German Neurological Society ([www.dgn.org](http://www.dgn.org)). The daily dosage of 5 g per day used in this study was in the upper range of the recommended dosages and, as expected from the safety-profile of Acetyl-DL-Leucine, well tolerated.

Although used for more than 50 years, the therapeutic mode of action of Acetyl-DL-Leucine has so far not been very well examined. It may act due to its direct effect on neurons as was shown in the vestibular nuclei [11]. Due to the phylogenetical and electrophysiological similarities and close interactions between vestibular and deep cerebellar neurons [12], we had hypothesized that there may also be a positive effect on ataxic symptoms in cerebellar disorders.

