#### **Analysis of key secondary endpoints:**

In case of a statistically significant primary efficacy result, confirmatory testing will be extended to the EQ-5D-5L (VAS and descriptive scale). Two-sided tests for detecting treatment differences will be carried out.

SCAFI (total score and 3 subscores), SARA subscale items, as well as patient-reported outcomes BDI-II and FSS are not considered in the hierarchical multiple testing procedures. Descriptive comparisons between treatment groups at the end of the 6-week verum/ placebo period will be performed by use of a two-sided Wilcoxon signed rank test, and additionally, Hodges-Lehmann estimation of the location shift between the two groups will be provided, as considered appropriate based on the blinded data. The same non-parametrical tests will be employed to estimate treatment differences at the follow-up visit 8 (close-out visit).

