**22.2 Ataxia score: SCAFI****SCA Functional Index – Case Report Form**

Rater (initials): \_\_\_\_\_

Proband-Pseudonym

Date of examination: \_\_\_\_\_

**Timed walking test: 8m walk (8MW)**☐ test not performed, reason: \_\_\_\_\_☐ proband unable to walk due to physical limitations

assistive device

☐ none☐ one cane /crutches☐ orthosis☐ two cane /crutches☐ wheeled walker

Did situations arise that necessitated repetition of a trial ( e.g. proband fell, external interference during walking, examiner forgot to start/ reset stopwatch) ?

Other factors that might have affected performance ?

Times are only given for two successfully completed trials.

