**Confidential**

---

Other factors that might have affected performance ?

---

Times are only given for two successfully completed trials for each hand

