**Timed speech task: PATA rate**

- ☐ PATA rate task not performed, reason: \_\_\_\_\_
- ☐ Proband unable to perform PATA rate task

Did situations arise that necessitated repetition of a trial ( e.g. proband coughing, external interference during testing, examiner forgot to start stopwatch/ tape) ?

---

Othe factors that might have affected performance ?

---

Counts are only given for two successfully completed trials.

|                                                                                                                                                                                                                          |                                                                                                                                                                                                                          |
|--------------------------------------------------------------------------------------------------------------------------------------------------------------------------------------------------------------------------|--------------------------------------------------------------------------------------------------------------------------------------------------------------------------------------------------------------------------|
| Trial 1

 
PATA_T1
 
 | Trial 2

 
PATA_T2
 
 |
|--------------------------------------------------------------------------------------------------------------------------------------------------------------------------------------------------------------------------|--------------------------------------------------------------------------------------------------------------------------------------------------------------------------------------------------------------------------|

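### Read literally, the SCAFI rule in section 10.1.1 inverts the PATA count, so a speech gain pulls the SCAFI total in the wrong direction

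*Protocol*

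**What the plan says.** Protocol section 10.1.1 describes the SCAFI as "evaluating the eight-meter-walking-time (8MW), the nine-hole-peg-test (9HPT) testing limb ataxia and the PATA-test for speech". It then gives the scoring in two steps. First, "raw scores are transformed into reciprocals and converted into subtest Z-scores". Second, "The final SCAFI is then generated as the arithmetic mean of all three Z-scores". Neither step treats PATA differently from the other two tests.

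The case report form in Appendix 22.2 fixes the raw units:

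- **8MW:** fields in 0.1 s, with the note "Times are only given for two successfully completed trials".
- **9HPT:** fields in 0.1 s, with the note "Times are only given for two successfully completed trials for each hand".
- **PATA:** headed as a rate, with no seconds unit on the fields and the note "Counts are only given for two successfully completed trials".

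Section 6.4 names the SCAFI total and its subscores as secondary efficacy endpoints. Section 13.1 sets their rank: "SCAFI (total score and 3 subscores), SARA subscale items, as well as patient-reported outcomes BDI-II and FSS are not considered in the hierarchical multiple testing"; they are compared descriptively.

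**The concern.** A mean of Z-scores makes sense only if all components point the same way. For a time, shorter is better, and the reciprocal turns it into a speed that rises with improvement. A PATA count already rises with improvement, so its reciprocal falls. The protocol does not say in words that a higher PATA is better, but a count of repetitions reported as a rate has no other natural reading. Section 5.1 also lists the PATA rate among the tests on which case-series patients did better.

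A programmer who follows 10.1.1 to the letter would build a total in which better speech counts as deterioration and offsets gains in gait and hand function. The same reversal would affect a PATA subscore Z derived by the same rule. If the programming uses a different rule without saying so, the analysis departs from the protocol's definition of an endpoint.

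**Working it through.** The protocol states no SCAFI effect, SD or target difference, so there is no planned figure to reproduce. The check is of direction first, then of size.

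**Direction** (from section 10.1.1 and Appendix 22.2)

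| Subtest | Raw unit | Better raw value | Reciprocal on improvement |
|---|---|---|---|
| 8MW | time | lower | rises |
| 9HPT | time | lower | rises |
| PATA | count | higher | falls |

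The reversal follows from the text alone.

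**Size.** Assume 8MW and 9HPT each improve by d SD and PATA by x·d SD. With weight 1/3 each, and treating the PATA reversal as a simple change of sign:

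- directions aligned: (d + d + x·d)/3 = d(2+x)/3
- as written: (d + d − x·d)/3 = d(2−x)/3
- share lost: 1 − (2−x)/(2+x) = 2x/(2+x)

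| x | Aligned (units of d) | As written (units of d) | Share lost |
|---|---|---|---|
| 0 | 0.667 | 0.667 | 0% |
| 0.25 | 0.750 | 0.583 | 22% |
| 0.5 | 0.833 | 0.500 | 40% |
| 2/3 | 0.889 | 0.444 | 50% |
| 1 | 1.000 | 0.333 | 67% |
| 1.5 | 1.167 | 0.167 | 86% |
| 2 | 1.333 | 0.000 | 100% |

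More than half is lost only if x exceeds 2/3. The sign is wrong only if x exceeds 2.

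**Check with actual reciprocals.** A reciprocal is not exactly a sign change, so the rule was also simulated with assumed log-normal raw scores (CV 0.2 to 0.4, correlation between subtests 0.3 or 0.6) and a 10% improvement in both speeds and in the count. At CV 0.3 the PATA Z-score moved by about +0.33 as a count and −0.30 as a reciprocal. The total moved by about 0.33 aligned and 0.12 as written. The loss was about 64% in every scenario, close to the 67% from the linear formula at x = 1.

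**What the protocol hints about x.** The only indication is the 13-patient case series in section 5.1: p = 0.003 (8MW), 0.011 (9HPT, dominant hand) and 0.005 (PATA). If these came from paired t-tests on 12 df, which the protocol does not say, then t = 3.71, 3.00 and 3.43. This gives x = 3.43 / [(3.71 + 3.00)/2] = 1.02 and a loss of 2 × 1.02/(2 + 1.02) = 68%. This is a rough pointer, not an estimate.

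**Standardised effect.** Reversing one component also changes the variance of the total. With equal effects (x = 1), equal variances and a common correlation r between subtest changes, the variance of the sum is 3 + 6r aligned and 3 − 2r as written. The share of the standardised effect retained is [1/√(3 − 2r)] / [3/√(3 + 6r)]: 33% at r = 0, 58% at r = 0.5 and 71% at r = 0.7. The loss of power is therefore smaller than the loss in the point estimate when the changes correlate.

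**The case against.** The strongest reply is that the sentence is a loose summary of a published, validated index that the protocol cites and gives no sign of wanting to alter. Section 10.1 presents itself as an overview. The reciprocal step neither says that every raw score is inverted nor names PATA, and the text just before it calls the approach timed, so one could read it as covering times only. Nor is it a complete algorithm: it gives no reference population for the Z-scores and no rule for combining trials or hands, so a programmer would need another source anyway.

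Part of this stands. The intent may well be right, and the cited scoring is not at hand to settle it. But the timed description is applied to the whole SCAFI, no subtest is excepted, and nothing elsewhere in the protocol limits the step. This is a derivation that the protocol does state, not a detail left for the SAP.

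Three stronger readings are tempting, and the documents do not support them:

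- **The rule cancels most of a real improvement.** This needs x above 2/3. The only support is the set of p-values from a small, uncontrolled series with an unstated test.
- **The total shows the wrong sign when all three tests improve.** This needs PATA to gain more than the two timed tests together (x above 2 when those are equal). Nothing in the protocol suggests it.
- **The trial's main conclusion is at risk.** The SARA analysis, the confirmatory EQ-5D-5L step and the sample size do not use the SCAFI. The subscores are analysed beside the total, and the raw times and counts are recorded, so a direction error could be found and corrected.

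**Conclusion.** The point holds as a defect of the wording: taken literally, section 10.1.1 gives PATA the opposite direction to the other two components, and nothing else in the protocol corrects it. That rests on the protocol text and on reading a higher PATA count as better.

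The size depends on an assumption about x that the protocol cannot settle. Across x from 0 to 2 the loss in the SCAFI total runs from nothing to all of the improvement, with two thirds lost if the three tests improve equally. The effect is confined to a descriptive secondary endpoint and to any PATA subscore derived in the same way. It merits correction because the rule gives a wrong result for a named endpoint, not because it threatens the primary result.

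**What to change.** In section 10.1.1, state that only the 8MW and 9HPT times are converted to reciprocals, that the PATA count enters its Z-score untransformed, and that a higher value means better for all three Z-scores before averaging. Any SAP or derivation program should use the same rule.

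The cost is a sentence or two. No data collection, sample size or primary analysis changes. It is best done before unblinding, so that the choice of direction cannot appear to depend on the results.
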